# Study design

We propose to conduct a trial with mothers in Lusaka district. This area was selected to ensure feasibility of the study. Lusaka is an urban area with relatively easy access to care and transportation.

This is a pilot study nested within the “THE IMPACT OF GROWTHCHARTS ON STUNTING AND CAREGIVER AWARENESS: RESEARCH AND POLICY ENGAGEMENT FOR POTENTIAL SCALING (REF. NO. 1411-2020)” clinical trial using a mix-methods analysis. 790 caregiver-child dyads were enrolled in this study in Lusaka in 2021; 30% of these women displayed mild to severe symptoms of depression and/or anxiety (SRQ-20 ≥ 8). For this feasibility study, we will randomly select women from this subgroup. All selected women will be contacted and reassessed with the Self-Reporting Questionnaire (SRQ-20) and further assessed using the Hopkins Symptoms Checklist-25 items^11-13^.

Final ***eligibility*** will be determined by 1) SRQ-20 >7 (clinically significant symptoms of depression or/anxiety anxiety), 2) women with 1 hour a week availability not planning to move within the next 6 months, 3) capacity to consent and 4) not receiving current mental health care. Individuals with active suicidal ideation (determined by Paykel scale^14^), severe substance use (ACOK-SUD >4),^15^ mania or psychotic symptoms^16^ will be excluded and referred to primary care provider or partnering psychiatrist (for emergency cases). We expect that around 70 caregivers will meet the inclusion criteria for the mental health feasibility study. All selected women from the intervention group will be contacted and reassessed with the Self-Reporting Questionnaire (SRQ-20) and the Hopkins Symptoms Checklist 25.

Eligible individuals will continue with a Baseline interview to assess main outcome measures. We plan to focus on engaging participants in each of the research components of the trial (assessments and sessions) through systematic engagement protocol including regular calls to participants and home visits after two weeks of non-responsiveness. All eligible subjects will be randomized with probability of 0.5 to either treatment or control group. Randomization will be based on a random draw generated by the senior author (GF) using the Stata SE 16.0 statistical software package.

Each enrolled participant will be assigned a specifically trained CHW, that we will call Wellbeing-Community Worker (WCW). WCWs will conduct a welcome call to their assigned participant and provide 10-12 individual sessions of the PM+FM intervention.

In a first step, we will assess efficacy by re-evaluating mental health symptoms (using HSCL-25) of caregivers again 5 months after the intervention. In a second step, we will compare changes in mental health at the population level using data from the larger study. Specifically, we will use endline data to be collected in the second quarter of 2023 to look at mid-term mental health outcomes (SRQ-20) as well as caregiver-child interactions and child developmental outcomes.

Qualitative data will be collected through semi-structured interview to participants during treatment completion assessment (5 months after enrollment) and focus groups with WCWs providing the intervention (analyzed using thematic approach to inform and complement quantitative results on feasibility, acceptability, and efficacy of the PM+FM intervention.

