| **Outcome (s)** | The primary study outcomes will be 1) number of sessions of PM+ attended (acceptance of the program = >50% of sessions attended; feasability within the local context = ≥ 1 session attended and offered and participants’ and providers’ qualitative feedback) and 2) improve their mental health status (overall mental health symptoms by SRQ-20 <7; Hopkins Symtpoms checklist reduction (% of cutoff <1.0.6),  Secondary outcomes: Patient Health Questionnaire (PHQ-9) (0-27; cutoff score, >10) for depressive symptoms; Generalized Anxiety Disorder Scale (GAD-7) score range, 0-21; cutoff score, >10) for generalized anxiety symptoms; Psychlops, psychological outcome profiles (designed to evaluate problem management plus intervention) and World bank toolkit on child-mother relationship. |
| **Study Design** | Randomised control trial |
| **Inclusion/Exclusion Criteria** | All mothers enrolled in Zamcharts clinical trial (n=790) with SRQ-20>7.  Exclusion criteria:   - Mothers who plan to migrate out of the study area within 6 months of the enrolment date - Mothers with severe substance use symptoms, bipolar disorder or squizophrenia - Mothers receiving psychotherapy elsewhere |
| **Measurements and Procedures** | From the total of 265 mothers residing in Lusaka district participating in the ZamCharts study and with mental health needs, we will divide them into two groups:  a control group a intervention group  All women will be called for a screening interview and then, if eligible, invited to receive a baseline interview followed by the intervention (provided in health facilities, by phone and at home) at the beginning and an endline interview at the end of the study.  Families in the intervention group will receive a locally adapted version of the Problem-Management Puls intervention developed by WHO after the baseline interview that allows them to better manage life stressors. The intervention will be provided by trained community health workers, started in groups (1^st^ session) and then continued individually by phone, or in-person at health facilities or at women’s home.  Severe cases will be referred to psychiatry services to evaluate need of antidepressants. |
| **Study Product/Intervention according to KlinV, if applicable** | This study will test an intervention: Problem Management+For Moms (PM+FM) program to reduce mental health symptoms among women and increase mother-child interaction |

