### Secondary endpoints

Secondary endpoints will be the psychological outcome profiles to measure women’s wellbeing and mother-child interaction and child early development.

| **Table 1. Measures and Outcomes** | **Measures Exploratory Efficacy Outcome** |
| --- | --- |
| **Screener measures** | Mania and Psychosis 4 question history (+ MDQ if positive), Capacity to consent (using a validated screening tool), ACOK (> 1 scores for MH and <3 SUD), Paykel suicidality risk scale -.  SRQ-20 >7 |
| **Primary Outcome Measures for EM-PM+ (assessed at enrollment, and 6 months** | |
| **SRQ-20** | 20 items measuring risk of common mental health problem. Used in the intent-to-treat analysis to explore effectiveness of the intervention using control group (endline data from parent study) |
| **Feasibility** | % of 1 or more sessions completed. Completion rates; ease/burden. Qualitative feedback from participants and providers. |
| **Acceptability** | 1) Participation rates; 2) Satisfaction scale; 3) Relevance of PM+FM. Qualitative feedback from participants and providers. |
| **Secondary Outcomes** | |
| **PSYCHLOPS** | Psychological Outcome Profiles (5 items) |
| **WHO-DAS2** | Functionality |
| **HSCL-25** | 10 questions anxiety, 15 depression; (α = 0.90). Used for the pre-post treatment analysis. |
| **World Bank’s** Toolkit **and** Inventory^17^ | Selected measures from the World Bank Toolkit to address mother-child interactions and child early development. |

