## Exclusion criteria

Women with active suicidal ideation (determined by Paykel scale^14^), severe substance use (ACOK-SUD >4),^15^ mania or psychotic symptoms^16^ will be excluded and referred to primary care provider or partnering psychiatrist (for emergency cases). Additionally, women planning to move in the next 6 months were excluded from the study.

We expect that around 70 caregivers will meet the inclusion criteria for the mental health feasibility study.

All eligible subjects will be randomized with probability of 0.5 to either treatment or control group. Randomization will be based on a random draw generated by the senior author (GF) using the Stata SE 16.0 statistical software package.

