## Description of statistical methods

First, we will begin with descriptive analysis of all data by site, using means, variances, quartiles, and graphical assessments of the distribution and skewness of the data. We will describe feasibility and acceptability measures at the participant level.

Then, we will proceed with a pre-post intervention analysis using the Hopkins Symptoms Checklist as a main outcome to compare mental health symptoms before and after receiving the intervention. Moreover, on a second phase, we will calculate effect sizes and trends of effectiveness between intervention group and the non-treated group from the parent trial using endline data from parent trial.

We will use standard linear regression models to assess the impact of the intervention arm on mother’s mental health and mother-child relationship. The intervention outcome variable will be SRQ-20 used as a dichotomous variable with the cutoff at seven. Separate models will be estimated with and without baseline covariates.

The feasibility, acceptability, and difficulties and successes in carrying out research and intervention activities will be explored through a mix-methods analysis including dosage analysis (attendance to the intervention’s sessions) and semi-structured interviews with the participants and focus group with intervention’s providers. The burden of completing the assessments and PM+FM on the time and effort of participants, satisfaction with the intervention, and barriers and facilitators to adherence will be explored through semi-structured interviews with all the participants enrolled in the intervention arm (including participants that have dropped out). Qualitative data resulting from the open-ended questions to participants and focus groups with WCHWs will be transcribed, coded and analysed using a thematic approach to inform on feasibility, acceptability, and explain the potential efficacy of the PM+FM intervention

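### The protocol does not consistently identify the control group for the efficacy comparison: this trial's randomised controls, or untreated women from the parent trial

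*Protocol*

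**What the plan says.** Three descriptions stand in the current text.

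- **A randomised control arm.** Study design says "All selected women will be contacted and reassessed with the Self-Reporting Questionnaire (SRQ-20) and further assessed using the Hopkins Symptoms Checklist-25 items". It then moves eligible women to baseline and randomises them. Exclusion criteria repeats the allocation rule: "All eligible subjects will be randomized with probability of 0.5 to either treatment or control group". The Synopsis (Measurements and Procedures) also screens everyone: "All women will be called for a screening interview and then, if eligible, invited to receive a baseline interview". The Comparator section gives controls no intervention.
- **An intervention group that exists before allocation.** Later in the same Study design paragraph, still ahead of the baseline and randomisation sentences: "All selected women from the intervention group will be contacted and reassessed with the Self-Reporting Questionnaire (SRQ-20) and the Hopkins Symptoms Checklist 25". The section goes on: "Each enrolled participant will be assigned a specifically trained CHW, that we will call Wellbeing-Community Worker (WCW", and provides sessions to that participant, with no exception for controls.
- **A comparator from the parent trial.** Description of statistical methods plans to calculate "effect sizes and trends of effectiveness between intervention group and the non-treated group from the parent trial using endline data from parent trial". Table 1, under Secondary endpoints, says SRQ-20 will serve the intention-to-treat analysis to "explore effectiveness of the intervention using control group (endline data from parent study". Study design describes the second efficacy step as a population-level comparison on the larger study's data.

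No section says that the parent trial's untreated group consists only of the women randomised to control in this trial.

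**The concern.** The protection against selection and confounding that Measures to minimize bias claims comes from randomisation. It holds only if the groups compared are the groups randomised. If only the intervention group is reassessed, or if controls are untreated parent-trial women taken from its endline, the entry conditions apply to one side only. These are SRQ-20 still above 7 at rescreening, no suicidal ideation, no severe substance use, no mania or psychosis, no current mental health care, availability and consent. Such controls could include women who had already recovered by the time of rescreening, and women whom this trial would have excluded.

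Two further parts of the plan would then not work as written. Datasets to be analysed uses baseline variables to check randomisation balance and to adjust models, but controls who were not reassessed would have no matching baseline. The Primary endpoint section combines SRQ-20 and HSCL-25 with an and/or, while Table 1 reserves HSCL-25 for the pre-post analysis. Controls with only the parent survey's SRQ-20 could not be classified on the HSCL-25 part.

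**Working it through.** **Step 1. What the power statement presumes.** Section 7.2 gives 100 analysed women per arm, 20 points at power 0.8 and 23 points at power 0.9. The Synopsis gives α = 0.05; two-sided is assumed. The control prevalence at endline is not stated, so it was varied, and 0.60 is shown.

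n per arm = [1.960·√(2p̄(1−p̄)) + z_power·√(p₁(1−p₁) + p₂(1−p₂))]² / (p₁−p₂)²

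- 0.60 against 0.40, power 0.8: [1.960·√0.50 + 0.842·√0.48]² / 0.04 = 3.877 / 0.04 = 96.9, so 97.
- 0.60 against 0.37, power 0.9: [1.960·√0.4996 + 1.282·√0.4731]² / 0.0529 = 5.138 / 0.0529 = 97.1, so 98.

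With 100 per arm the powers are 0.812 and 0.908. The stated figures reproduce for a plain comparison of two equal arms. Section 7.2 therefore fits the randomised 1:1 design.

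**Step 2. The statements side by side.**

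| Place | Who is screened or enrolled | Comparator |
| --- | --- | --- |
| Study design, selection sentence; Synopsis | All selected women; all women | – |
| Study design, later sentence | Intervention group only, before allocation | – |
| Study design and Exclusion criteria, randomisation | All eligible women | Randomised control, 1:1 |
| Study design, WCW sentence | Every enrolled woman gets a WCW and sessions | No enrolled control left |
| Study design, second step | – | Population level, larger study's data |
| Table 1, SRQ-20 | – | Control group, parent endline data |
| Description of statistical methods | – | Parent trial's untreated group |
| Datasets to be analysed; Primary Analysis | – | Presume randomisation and intention-to-treat |

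The second and fourth rows cannot both hold with the third. The fifth to seventh rows agree with the third only if a restriction to randomised controls is read into them.

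**Step 3. Illustration of unequal rescreening.** Each woman's score at 2021, rescreening and endline is t + e, with Var(t) = r, Var(e) = 1 − r and independent errors. The cut-off is set so that 30% are positive (Study design). There is no treatment effect, and 2 million women were simulated. The retest correlation r is an assumption; the documents give none. Entries are endline prevalence of SRQ-20 above the cut-off.

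| r | Positive in 2021 and at rescreening | Positive in 2021, not rescreened | Difference |
| --- | --- | --- | --- |
| 0.3 | 51.9% | 42.7% | 9.2 points |
| 0.5 | 64.3% | 52.3% | 12.0 points |
| 0.7 | 75.7% | 63.6% | 12.1 points |

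If both arms are rescreened and then randomised, the expected difference is 0. If only the intervention arm is rescreened, it appears 9 to 12 points worse with no true effect. That is 9.2/20 = 46% to 12.1/20 = 61% of the stated detectable difference.

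**The case against.** The strongest reply is that the parent endline is only the data source for the randomised controls. Every participant is a parent-trial mother, so the control arm is naturally an untreated group from that trial. Table 1 and Primary Analysis say intention-to-treat, Datasets to be analysed refers to balance through randomisation, and the randomisation rule is stated twice. This reading may well be what is intended, and the bias is conditional on its being wrong. It does not remove the point, because the methods section never names the randomised control arm and two Study design sentences contradict the randomised flow.

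The efficacy analysis is also exploratory by section 7.2, and the feasibility and acceptability measures need no control group. Both are correct and limit what is at stake.

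Four stronger readings are not supported:

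- A reader might infer that the Synopsis allocates before screening, since it mentions dividing the mothers first. It screens all women and takes only eligible ones forward, so it does not produce unscreened controls.
- A reader might divide the 70 expected eligible women by the number of positives and conclude that about 70% of unscreened controls would be ineligible. Study design says women are randomly selected from the positives and does not say how many, so the denominator is unknown.
- A reader might take the comparator to be all parent-trial women. In the illustration their endline prevalence is 30%, a gap of 22 to 46 points (51.9 − 30.0 to 75.7 − 30.1). The population-level wording is undefined and does not establish this.
- A reader might infer that controls are measured in a different survey. Study design does not restrict the parent endline to controls, so both arms may be measured in it.

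**Conclusion.** The control group for the efficacy comparison is not consistently identified, and the text needs correcting. As written, it permits a non-randomised, unequally screened comparison in a trial described as randomised, contrary to Measures to minimize bias, Datasets to be analysed and Primary Analysis. Whether that comparison would actually be made cannot be told from the protocol.

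The 9 to 12 points are an illustration and not an estimate of bias. They rest on assumed retest correlations of 0.3 to 0.7, a normal latent score, 30% positive and no treatment effect, and they cover rescreening on SRQ-20 alone. The exclusions for suicidal ideation, substance use, mania or psychosis and current care could remove more severe women and pull the other way. The net size and direction cannot be fixed from the documents.

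**What to change.** State one flow: rescreening, consent and baseline (SRQ-20 and HSCL-25) for every selected woman, then 1:1 randomisation of the eligible. To make the text agree:

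1. In Study design, delete the words that restrict the second reassessment sentence to the intervention group.
2. In Study design, limit the WCW assignment and sessions to women randomised to PM+FM.
3. In the second efficacy step of Study design, in Table 1 (SRQ-20) and in Description of statistical methods, name the randomised control arm of this trial, analysed as randomised, as the comparator.
4. Use the parent endline survey for the comparison only if both arms are measured in it in the same way, and say so.

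In the Synopsis, moving the division into two groups after eligibility is only a clarification.

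The cost is protocol wording. No stated sample size changes, and the Synopsis already plans screening for all women and a baseline interview for the eligible.

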| **Comparator(s) (if applicable)** | The comparator for the interventions is standard local caregiving (no intervention) among mothers participating in the Zamcharts clinical trial |
| **Study Duration** | 9 Months |
| **Participants** | A total of 265 caregivers and their children are expected to participate in the study. |
| **Study Schedule** | Sept. 2022: study setup, software development and IRB approval. Identification of WCW  Sept. 2022 – Nov. 2022: Training of 3-5 WCW  Nov. 2022: Enrollment of participants. Screening.  Dec. 2022 – April 2023: implementation of interventions  April 2023: Endline assessments  May 2023 - December 2023: Data analysis & dissemination |
| **Study Centre(s)** | The study will be coordinated by the PIs, and implemented by Innovations for Poverty Action Zambia in direct collaboration with the Zambian Ministry of Health and the department of psychiatry of the University Teaching Hospital in Lusaka. |
| **Statistical Considerations & Power calculations** | The study is statistically powered to detect a 0.25 SD improvement in SRQ-20 over an 6-month period between mothers receiving the PM+FM and mothers not receiving the intervention, assuming α=0.05, a follow-up rate of 85% (attrition < 15%), and an intra-class correlation coefficient (ICC) of 0.05 . The estimated improvement is based on the results from similar studies. |
| **Ethical Statement** | This study will be conducted in compliance with the protocol, the current version of the Declaration of Helsinki, KFPE principles for transboundary research as well as all national legal and regulatory requirements. |

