## Primary and secondary endpoint

### Primary endpoint

The primary endpoint will be SRQ-20 = or < 7 6 months after enrollment in the trial and/or HSCL-25 <1.06 6 months after enrollment.

We will also collect data on attendance rates to assess feasibility and acceptability throughout the deployment of the intervention:

- Feasibility will be assessed by the percentage of participants completing 1 or more sessions of the intervention and through a focus group with the intervention providers.
- Acceptability will be evaluated using the percentage of participants completing the program (≥50% sessions completed) together with qualitative feedback from participants and providers through a semi-structured interview at the end of the intervention and participants’ feedback from a semi-structured interview at the end of the intervention.

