## Study duration and duration of participant’s participation

The project will be divided into three phases: A preparatory phase (Month 1 - 6) will primarily focus on developing and adjusting the intervention, and for piloting field logistics. This initial phase will be followed by a trial phase (Month 7-12) and a final analysis and dissemination phase (year 2).

We anticipate to start identification cases, screening and enrollment to the trial in October- Nov. 2022. An Endline assessment will be conducted approximately 5 months after completion of the baseline survey (April 2022).

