### Schedule of events

Table 1. Project Milestone

| Date | Description |
| --- | --- |
| July 2022 – Sept. 2022 | Study setup, IRB approval, identification of WHW, |
| Sept. 2022 – Oct. 2022 | Training of 4-6 WCW. Identification of participants (Screening) |
| Nov. 2022 – Mar 2023 | Baseline and Intervention period |
| May 2023 - June 2023 | Endline assessments |
| Jul 2023 – Sept. 2023 | Data analysis |
| Oct. 2023 – Dec. 2023 | Study dissemination |

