## Identity of investigational products

### Experimental intervention (treatment / medical device)

To develop the PM+FM intervention, we followed the Castro-Barrera framework for cultural adaptation of evidence-based interventions. ^23^ Therefore, the intervention is culturally adapted to women’s local context of social and cultural values and norms.

This study aims at assessing one intervention: Problem Management Program-For Moms

**Intervention:** The PM+FM intervention is a cognitive-behavioral therapy-based transdiagnostic psychosocial intervention using a context-adapted version of the PM+ manual from WHO and specific sections from the Strong Minds psychosocial intervention and psychoeducation material from a psychosocial stimulation intervention in early childhood to improve women’s wellbeing including mental health symptoms and mother-child relationship. The intervention:

- Is provided individually, organized in 10 to 12 1-hour sessions and provided on a weekly basis by a specifically trained and supervised WCW in women’s homes.
- Lasts a maximum of 5 months. Following regular clinical patterns of attendance, participants can schedule the sessions within this period to finish the program.
- Will be culturally adapted to women’s local context of social and cultural values and norms using a systematic cultural adaptation framework. To develop the PM+FM intervention, we followed the Castro-Barrera framework for cultural adaptation of evidence-based interventions.^18^ Therefore, the intervention is culturally adapted to women’s local context of social and cultural values and norms.
- Follows a collaborative and patient-centered approach where individual’s needs are central and contents of the intervention are adapted to each person.
- Combines psychoeducation, problem-solving and cognitive restructuring techniques, motivational interviewing approach, effective communication practice and mindfulness practice.

| **PM+FM Intervention summary of contents** | |
| --- | --- |
| Session 1 | Symptom’s assessment. Introduction of the program and confidentiality. Cultural Formulation interview to understand woman’s need. Psychoeducation about mental health needs (understanding adversity) and maternal-child positive relationship. Relaxing breathing. |
| Session 2 | Barriers to change, managing problems and stress management strategies. Introduction to mindfulness. |

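### The protocol sets the primary mental health outcome at 6 months after enrolment, but its design narrative and schedules give other times, including an endline at about 5 months while some women may still be in treatment

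*Protocol*

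**What the plan says.** Three places agree on 6 months:

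- Primary endpoint section: "The primary endpoint will be SRQ-20 = or < 7 6 months after enrollment in the trial and/or HSCL-25 <1.06 6 months after enrollment".
- Table 1, heading of the primary outcome measures: "assessed at enrollment, and 6 months".
- Synopsis power statement: improvement in SRQ-20 over a 6-month period.

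The other places give different times:

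- Study design, on HSCL-25: "we will assess efficacy by re-evaluating mental health symptoms (using HSCL-25) of caregivers again 5 months after the intervention". The same paragraph takes SRQ-20 from the parent study's endline in the second quarter of 2023. The next paragraph places an end-of-treatment assessment 5 months after enrolment.
- Study duration section: "An Endline assessment will be conducted approximately 5 months after completion of the baseline survey (April 2022"). The same section opens screening and enrolment in October to November 2022.
- Synopsis schedule: "April 2023: Endline assessments", with the intervention running from December 2022 to April 2023.
- Milestone table (Schedule of events): endline in "May 2023 - June 2023", after a combined baseline and intervention period of November 2022 to March 2023. Data analysis follows in July to September 2023.

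On treatment length, the intervention section says that the programme "Lasts a maximum of 5 months".

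**The concern.** An effect measured while some women are still attending sessions, an effect about a month after the longest permitted course, and an effect five months after treatment ends answer different questions. The field team has to book the endline from one rule, and the protocol offers several. If the synopsis schedule is followed, the 6-month endpoint is not what gets measured for women enrolled in November. If the Study design sentence is followed literally, HSCL-25 is collected after data analysis is due to have begun. Once the endline has been held at the wrong time, the intended 6-month measurement cannot be recovered.

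**Working it through.** The check is calendar arithmetic in whole months, using only the protocol's dates. The reference case is a woman with baseline and enrolment in November 2022, the enrolment month in the synopsis and the first baseline month in the milestone table.

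**The protocol's own date.** The duration section puts the endline about 5 months after baseline and prints April 2022. October 2022 + 5 = March 2023; November 2022 + 5 = April 2023; December 2022 + 5 = May 2023. None gives April 2022, which is 6 to 7 months before enrolment opens. April 2023 fits a November baseline, so the printed year is evidently a slip for 2023.

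**Each stated time, for a November 2022 baseline**

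| Source | Rule or date | Calendar result | Months since baseline |
|---|---|---|---|
| Primary endpoint, Table 1 | enrolment + 6 | May 2023 | 6 |
| Study duration | baseline + 5 | April 2023 | 5 |
| Synopsis schedule | fixed date | April 2023 | 5 |
| Study design, SRQ-20 | second quarter 2023 | April to June 2023 | 5 to 7 |
| Milestone table | fixed dates | May to June 2023 | 6 to 7 |
| Study design, HSCL-25, read literally | end of intervention + 5 | March + 5 = August 2023 (milestone table), or April + 5 = September 2023 (synopsis) | 9 to 10 |

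Without the last row the range is 5 to 7 months. With it, the range runs from 5 to 9 or 10 months, a spread of 4 to 5 months. August and September 2023 both lie inside the July to September analysis period.

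**Can an April 2023 endline fall during treatment?** On the synopsis schedule, a woman starting in December 2022 reaches April 2023 at month 4. The 5-month maximum lets her continue to about May 2023, so she can still be in sessions. At the planned weekly pace, 10 to 12 sessions take 10/4.345 = 2.3 to 12/4.345 = 2.8 months (4.345 weeks per month). The overlap therefore concerns women who use most of the permitted period, not those who attend every week.

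**Which calendar serves the 6-month endpoint?** November 2022 + 6 = May 2023 and December 2022 + 6 = June 2023, so the milestone table's May to June endline fits enrolment in those two months. April 2023 is month 6 only for a woman enrolled in October 2022; it is month 5 for November and month 4 for December.

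**The case against.** The strongest reply is that the endpoint is defined, and consistently: the endpoint section, Table 1 and the power statement all say 6 months. The conflicts lie in narrative text and calendars. Most of the dates also overlap, since the second quarter of 2023 contains both endline schedules and the 6-month date for a November enrolment. The phrase that reaches August to September may be loose wording for 5 months after the intervention starts. The next paragraph of Study design, and an endline that closes in June, support that reading. Only the synopsis overlaps endline with treatment; the milestone table leaves a gap. The sample size section also presents efficacy as exploratory.

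Most of this stands, and it limits the size of the problem. It does not remove it: 5 and 6 months cannot both be right, nor can April and May to June, and the April date does not deliver the stated endpoint for women enrolled in November.

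A reader might go further and infer that the two arms will be measured at different times since baseline, so that natural remission distorts the comparison. The documents do not support this. Table 1 and the statistical methods section assign HSCL-25 to the pre-post analysis, which has no control contrast. The between-arm SRQ-20 comparison uses the parent-trial endline, collected in one stated quarter. No passage prescribes a gap between arms, and the protocol gives no remission rate, so any figure for such a bias would be assumed.

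**Conclusion.** The protocol contradicts itself on when the primary mental health outcome is measured, and the text needs reconciling before the endline is scheduled. For a November 2022 enrolment the conflict is mainly 5 against 6 to 7 months. It extends to 9 to 10 months only if the single HSCL-25 sentence is taken literally. That extreme matters for the primary outcome only because the endpoint section includes HSCL-25; Table 1 lists the scale as secondary, which is a separate inconsistency. The practical consequence is specific: an April 2023 endline falls a month short of the stated endpoint and can reach women still in treatment.

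The month counts assume enrolment in November 2022 and whole-month arithmetic. It would be too strong to say that the primary outcome has no defined time, since the endpoint section gives one, or to count April 2022 as a rival assessment date. The power figures do not depend on this point.

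**What to change.** Make 6 months after enrolment, as the endpoint section and Table 1 already have it, the single primary assessment time for both arms and both scales, whether or not a woman has finished her sessions. Then align the rest:

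- Synopsis schedule: replace the April 2023 endline.
- Study design: replace the HSCL-25 timing counted from the intervention, and state how the parent-trial endline in the second quarter of 2023 supplies the 6-month SRQ-20.
- Study duration: change about 5 months to 6, and correct the year in April 2022.
- Milestone table: keep May to June 2023 if enrolment falls in November to December 2022, and adjust it if enrolment falls outside those months.
- State that both arms are assessed in the same window. Its exact width can be left to the statistical analysis plan or the study manual.

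The cost is wording, minor rescheduling of the endline and possibly some contacts outside the parent-trial endline survey, because SRQ-20 is drawn from that survey and its dates may not meet every woman's 6-month date.
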